## Methods: participants, interventions, and outcomes

### Study setting {9}

The study will be conducted in 24 districts across six regions of Uganda (four districts in each region—Fig. 2). The regions and districts include those not previously reached in pilot trials of the REAL Fathers intervention and are as follows:1) Ankole Region: Ibanda, Mbarara, Isingiro, and Rubirizi districts [Implementing Partner: FAWE Uganda Chapter]2) Buganda Region: Kayunga, Buikwe, Luweero, and Nakasongola districts [Somero Uganda]3) Bunyoro Region: Hoima, Kikuube, Kiryandongo, and Masindi districts [Bantwana Initiative Uganda]4) Busoga Region: Kamuli, Bugiri, Iganga, and Mayuge districts [Somero Uganda]5) Lango Region: Dokolo, Kole, Lira, and Oyam districts [All Nations Child Development Centre]6) Teso Region: Amuria, Katakwi, Serere, and Soroti districts [Bantwana Initiative Uganda]

**Fig. 2 Fig2:**
[figure not shown]
REAL Fathers implementing districts in Uganda

Community and village leaders within these 24 districts will be contacted by implementing partner staff (i.e., staff of the not-for-profit community-based organizations leading the implementation of the REAL Fathers intervention) to share information about REAL Fathers and to gauge the community leaders’ interest in and support for the intervention.

### Eligibility criteria {10}

Trial eligibility will be based on a two-stage screening process. In stage 1, project officers of the implementing partner organizations will contact local leaders (e.g., local civil servants, clan leaders, religious leaders) to share information about REAL Fathers and to generate a list of communities expressing interest in and support for their communities to become involved in REAL Fathers. In stage 2, the research team will conduct a listing/census exercise within the interested communities to identify all young men between the ages of 16 and 25 years. As summarized in Table 2, trial-eligible young men will be between the ages of 16 and 25 years; a permanent resident of the village; able to speak English or one of the six local languages; cohabitating with or married to a female partner; and have at least one child who is not over the age of three years. Only couples where both the father and his female partner consent to participate will be eligible to participate in the study.

**Table 2 Tab2:** Inclusion criteria by respondent type

		**Male respondents**	**Female respondents**
1	Between the ages of 16 and 25 years	✓	*No age restriction*
2	Permanent resident of one of the 24 districts (i.e., not a migrant or refugee)	✓	✓
3	Speaks English or one of the local languages (Runyoro, Langi, Luganda, Lusoga, Runyakitara, Ateso)	✓	✓
4	Biological parent to a child(ren)	✓	*Can be a guardian*
5	Oldest biological child under the age of 3 years	✓	✓
6	Living in the same household with the child(ren)	✓	✓
7	Living in the same household with the other parent (or guardian) of the child(ren)	✓	✓
8	Living in union with the mother of the child(ren) intimate partner	✓	*NA*
9	Spouse/partner consented to participate	✓	✓

### Who will take informed consent? {26a}

Given REAL Fathers emphasizes the role of fathers, we will first assess the eligibility of fathers in screening interviews. Eligible fathers will be invited to participate in the study and subsequently scheduled to participate in an interview. After fathers are invited and consented, their female partners will subsequently be invited to participate. All respondents will provide digital signature on the data collection tablets. A model consent form that will be programmed into KoboCollect is provided in the Appendix.

### Additional consent provisions for collection and use of participant data and biological specimens {26b}

This trial does not involve collecting biological specimens for storage.

## Interventions

### Explanation for the choice of comparators {6b}

Random allocation is made between intervention and wait-list control groups, as randomized at the sub-county level. The intervention group will receive the REAL Fathers intervention within a month after the screening process, while the wait-list control group will receive the REAL Fathers intervention after follow-up data collection (wave three) is conducted. Participants in the control group will continue to access standard care and services that are already available in their communities. These include the following: village health team visits and referrals to clinics when applicable; early childhood development centers and programming; family planning and social-economic interventions from Government, as described in further detail in the “Plans to promote participant retention and complete follow-up” section below.

### Intervention description {11a}

In acknowledgement of the critical nature of community support for the implementation of the REAL Fathers intervention, the depiction of the REAL Fathers intervention timeline in Fig. 3 includes a set of preparation activities that precede the mentoring components of the intervention, but that are integral to laying the groundwork for successful mentorship: community sensitization and engagement; adaptation of materials to the local context; and training of local community members. The second phase, Implement, Support, and Monitor, involves one-to-one and group mentoring of fathers, their spouses, community engagement and support, and adaptive management and complexity-aware monitoring.

**Fig. 3 Fig3:**
[figure not shown]
The REAL Fathers intervention at a glance

Phase 1 involves community sensitization, awareness, and advocacy meetings to learn about the intervention at either the village or parish level. Meetings cover what the REAL Fathers intervention does and aims to do, the target population, objectives and community roles, and eligibility criteria for participation in the intervention. In such meetings, some young fathers who fit the criteria are naturally identified and volunteer to be recruited. Other young fathers are identified by people in the meeting who they think fulfil the criteria. These young fathers are contacted by the project officers for further screening and recruitment into the intervention. After identifying interested young fathers, the young fathers are asked to nominate older fathers in their communities who they view as upstanding citizens and respected role models. Prospective mentors are contacted, informed of the study, and invited to participate. After selection, mentors undergo a five-day training on a variety of topics, as summarized in Table 3.

**Table 3 Tab3:** Content for training of mentors

Topic	Session
**Understanding REAL Fathers, Early Childhood Development and Trainer skills**	Introductions, ground rules and agenda
	Training of Trainer competencies and skills
	Introduction to REAL Fathers and Research Study
	Introduction to Early Child Development
	Components of Nurturing Care for Child Development
	Child Development Stages & Developmental Needs of a Child
**Understanding Values and Norms**	Gender Values Clarification
	Gender Roles and Household Decision-Making
	Gender Norms: Behave Like a Man, Behave Like a Woman
	What Kind of Husband and Father Am I?
**Happy Fathers, Happy Children**	Tips and Tricks to Being the Best Father in the Village
	In It to Win It: How Fatherhood Is Like Football
	Disciplining Your Child with Love
	From My Child’s Perspective
	The Invisible Wall
	Things Your Child Needs to Hear You Say
**Happy Homes: Living in Peace**	Why Do We Act This Way?
	Dealing with Stress and Managing Our Emotions
	Don’t Talk to Me That Way!
	Stronger Couples through Communication
	Good Sportsmanship: How the Rules of Marriage Are Similar to a Game of Football
**Safeguarding**	Definition and Examples of Abuse in Mentor–Mentee Relationships
	Safe Mentorship: Preventing Abuse and Referral Process
	Legal and Cultural Contexts of Safeguarding
	Mentor Code of Conduct
**Practicum: Putting It All Together**	Home Visit Protocol
	Home Visits with Young Fathers
	Home Visits with Couples
	Group Meetings Discussion Guide
	Women’s Group Session Guide

Following successful completion of the 5-day training, mentors then work directly with the young fathers who nominated them as mentors (up to 3 fathers per mentor) to provide 7 monthly individual and group mentoring sessions (one individual and group session per month), lasting roughly 1 to 1.5 h each. The mentoring sessions cover similar topics as those covered in the mentor training (see session titles in Fig. 3, with full details on session curricula provided elsewhere [47]). These individual, couple-, and group-based mentoring sessions are coupled with a community poster campaign and community celebration at the end of the seven sessions to model alternative strategies for nonviolent discipline and conflict resolution to improve fathers’ parenting and communication skills and confidence in adapting nonviolent strategies. The intervention is being implemented by four Uganda- and community-based organizations that are independent of the evaluation team. These include the following: Somero Uganda; All Nations Child Development Centre; Bantwana Initiative Uganda; and Forum for African Women Educationalists Uganda Chapter.

### Criteria for discontinuing or modifying allocated interventions {11b}

Given the nature of the intervention, we do not anticipate adverse events related to its delivery that will lead to termination of the trial. As such, there are no criteria in place for trial termination or for modifying intervention allocation. The REAL Fathers Consortium will apply responsive feedback mechanisms as outlined elsewhere [48], to allow systematic modifications to the intervention components between cohorts. These cohort effects will be accounted for in subsequent difference-in-differences analyses.

### Strategies to improve adherence to interventions {11c}

Adherence to the intervention (i.e., implementation fidelity, the degree to which the intervention is delivered as intended) will be assessed and supported through ongoing monitoring data collection by both the mentors and the implementing partner staff via a series of monitoring tools. Mentors will collect data on participation of fathers in the individual and group sessions, as well as the quality of the session. Mentors will also have access to the fathers’ phone numbers to help facilitate scheduling and follow-up.

Implementing partner staff will engage in regular check-in meetings with the mentors during the mentoring sessions to not only document what the mentors cover in the session, but to also provide supportive supervision and engage in standardized feedback on the session to improve implementation fidelity. All data will be uploaded to an online Monitoring Information System (MIS), with reports generated to respond to specific monitoring indicators. Using the MIS reports, the Monitoring and Evaluation officers at each implementing partner (IP) will review the monitoring data collected each month and provide monthly monitoring updates to the IP management.

Routine Data Utilization meetings will be held by the M&E officers at each implementing partner among all project officers to engage in review of the data and dialogue on the realities experienced in the communities that reflect what’s shown in the data. This regular exchange will encourage program officers to ensure each monthly session is being delivered as intended and to identify specific mentors or communities that may need additional support. Project officers will also meet with mentors on a monthly basis to conduct supportive supervision exercises and to provide feedback on the extent to which the mentors delivered the session material as planned. Finally, although no financial incentives are provided to the mentors, social status will be gained via increased visibility in the community and involvement in local leadership. This elevation in status of the mentors will incentivize the mentor fathers to stay continually active in their mentoring activities.

These reports will provide regular updates on the progress of each implementing partner on maintaining adherence to the protocol and schedule of the intervention. In addition, the managing organization will conduct routine supportive supervision for the implementing partners to review progress and provide feedback on areas for improvement. In the event that a mentor and/or the fathers are not engaging in the intervention material as planned, meetings will be set to follow up with the mentors and fathers to understand the challenges they may be facing.

### Relevant concomitant care permitted or prohibited during the trial {11d}

No concomitant care prohibited.

### Provisions for post-trial care {30}

Not applicable; no risk of harm anticipated; no provisions prepared. In the event of potential harm, participants will be encouraged by mentors to seek support from health and social workers trained in violence prevention and harm reduction.

### Outcomes {12}

This trial is designed to assess differences in the specified outcome measures between the intervention and waitlist control groups at endline and follow-up. All primary and secondary outcomes will be assessed at three points: (1) Baseline, one month before the intervention; (2) Endline, one month after the intervention ends (nine months after the baseline survey); and (3) Follow-up, 9 months after the intervention ends (17 months after the baseline survey).

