**Methods:**

To assess the REAL Fathers intervention, we use a cluster-randomized controlled trial design within 48 sub-counties randomly sampled from 24 districts in six regions of Uganda. Sub-counties were randomly allocated to treatment or control arms at baseline. Study participants are fathers ages 16–25 years and their cohabitating wives whose eldest child is below the age of 3 years (*n* = 3744 couple dyads). Primary outcomes are the following: (1) reduced intimate partner violence; (2) reduced violent discipline of children; (3) increased father-child engagement and play; (4) improved early childhood development. Secondary outcomes include the following: (1) father’s knowledge of and (2) attitudes towards positive parenting and discipline; (3) father’s use of positive parenting and discipline; (4) father’s use of emotional engagement with child; (5) couple communication and conflict resolution; (6) gender equitable household and caregiving decision-making and behaviors; (7) father engagement in child health-promoting activities; (8) improved knowledge of family planning methods; (9) reduced unmet need for family planning; (10) reduced problem alcohol use; and (11) supportive community norms for father-child engagement and play. Longitudinal survey data will be collected by trained enumerators using KoboCollect in six local languages at three time points: one month before the intervention (baseline); one month after the intervention (endline); and nine months after the intervention (follow-up). Intervention effects on primary and secondary outcomes will be assessed using difference-in-differences (DiD) mixed-effects models that account for the clustered design.

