#### Primary outcomes

The study’s primary outcomes (Table 4) are reductions in intimate violence, violence against children, increased father-child engagement (early stimulation), and improvements in early childhood development outcomes.

**Table 4 Tab4:** Summary of primary outcome measures

Primary outcome	Measure description	Questionnaire
Intimate partner violence (IPV): Perpetration and Victimization	Proportion of young fathers and their wives reporting perpetrating or being a victim of physical, sexual, and/or emotional IPV in the past three months. Assessed via six measures: insulted; shouted or yelled; slapped; pushed or shoved; threw something at that could hurt; physically forced unwanted sex	Male and Female caregiver
Harsh violent discipline of children	Proportion of fathers reporting they used a form of harsh/violent discipline with their child in the past month. Items include the following: shook child; shouted, yelled at, or screamed at child; spanked, hit, or slapped child on the bottom with bare hand; hit child on the bottom or elsewhere on the body with something like a belt, stick, or other hard object; hit or slapped child on the face, head, or ear; hit or slapped child on the hand, arm, or leg; beat child up, that is, hit him/her over and over as hard as you could	Male
Fathers’ increased use of child engagement (early stimulation) activities	Proportion of fathers reporting use of early learning and play activities with child (i.e., stimulation activities). Activities include the following: reading, telling stories, singing songs, taking child outside of the home, naming/counting things together, drawing things together, playing with a toy or object	Male
Early childhood development	Scores on the short-form version of the Caregiver Reported Early Development Instruments (CREDI) [46]	Male and Female

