### Participant timeline {13}

This cRCT will roll out in a phased manner in conjunction with the larger implementation project using a subsample of individuals in three of the five implementation groups included as the intervention group in the trial. Sufficient time is planned to allow waitlist controls to transition to intervention groups in subsequent implementation rounds after they participate in the follow-up assessment. As shown in Table 6, for each trial cohort, baseline data collection will occur roughly one month before the start of a cohort, with endline data collection occurring roughly 8 months later (i.e., one month after the REAL Fathers intervention group ends). Follow-up data collection will occur 8 months after endline data collection.

**Table 6 Tab6:** Trial schedule: Enrolment, intervention, and assessments (adapted from SPIRIT 2013 Figure [36])

Date	Trial activity	Intervention activity		Cohort		
		REAL Fathers	Standard care	1	2	3
Nov 2023	Cohort 1 (C1) enrolment: eligibility screen and informed consent	Community engagement and sensitization (Steps 1–3)		1		
Dec 2023	C1 baseline assessment	REAL Fathers materials adaptations (Step 4) & Training of trainers (Step 5)		1		
Dec 2023 (after baseline)	Randomization (allocation to control or intervention)	Selection and training of mentors; selection of fathers (Steps 6–9)	x	1		
Jan–Aug 2024		Individual and group mentoring; community posters (Steps 10–11)	x	1		
Oct–Nov 2024	C1 endline assessment (1 mo. after intervention ends)			1		
Dec 2024–Jan 2025		Pause and Reflect				
Jan–Feb 2025	C2 enrolment: eligibility screen and informed consent	Community engagement and sensitization (Steps 1–3)			2	
Feb–Mar 2025	C2 baseline assessment	REAL Fathers materials adaptations (Step 4) & Training of trainers (Step 5)			2	
Mar 2025 (after baseline)	Randomization (allocation to control or intervention)	Selection and training of mentors; selection of fathers (Steps 6–9)	x		2	
Apr–Nov 2025		Individual and group mentoring; community posters (Steps 10–11)	x		2	
Jul 2025	C1 follow-up assessment			1	2	
Dec 2025	C2 endline assessment (1 mo. after intervention ends)				2	
Jan 2026	C3 enrolment: eligibility screen and informed consent	Community engagement and sensitization (Steps 1–3)				3
Feb 2026	C3 baseline assessment	REAL Fathers materials adaptations (Step 4) & Training of trainers (Step 5)				3

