Feb 2026 (after baseline)	Randomization (allocation to control or intervention)	Selection and training of mentors; selection of fathers (Steps 6–9)	x			3
Mar–Oct 2026		Individual and group mentoring; community posters (Steps 10–11)	x			3
Aug 2026	C2 follow-up assessment				2	
Nov/Dec 2026	C3 endline assessment (1 mo. after intervention ends)					3
June 2027	C3 follow-up assessment					3

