Since all trial outcomes are binary, we will use mixed-effects logistic regression models for the primary endline analysis. As a supplementary analysis, we will estimate causal effects in terms of risk differences using mixed-effects linear models, implemented via the *xtdidregress* and *xtreg* commands in Stata. Individual-level observations will be analyzed rather than cluster-averaged data, following methodologies outlined by Hussey & Hughes (2007) and Baio et al. (2015)) [54, 55]. Let $${Y}_{ijk}$$ denote an outcome of individual *i* from *j*th subcounty and *k*th region measured at time period *t*, and modelled as:$$logit(P({Y}_{ijkt}=1)={\beta }_{j}+\lambda {G}_{i}+\alpha {T}_{i}+\gamma {(GT)}_{i}$$where $${\beta }_{j}$$ is the random effects term for the sub-counties (with $${\beta }_{j} \sim N\left(0,{\tau }_{\beta }^{2}\right)$$.); $$\lambda$$ is fixed effect of randomization group (G_*i*_ = 1, if exposed to intervention; and G_*i*_ = 0, otherwise); $$\alpha$$ is a fixed effect of time (T_i_ = 0 if baseline, T_i_ = 1 if endline), and $$\gamma$$ is an interaction effect of time and group. Predicted margins will be used to compute the average causal effect or equivalently the ITT estimand.

For follow-up analysis, we will implement a three-time-point panel model to assess the persistence of treatment effects nine months post-intervention closure. Additionally, a two-time-point analysis (comparing endline and follow-up) will be conducted as a sensitivity analysis to evaluate short-termeffects.

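### Table 6 does not deliver the uniform one-month endline and nine-month follow-up stated in the text: by month labels, follow-up falls 11, 9 and 8 months after mentoring in Cohorts 1, 2 and 3

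*Protocol article*

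**What the plan says.** The text of the protocol article gives one timing for all cohorts. Outcomes {12} has "Endline, one month after the intervention ends (nine months after the baseline survey" and "Follow-up, 9 months after the intervention ends (17 months after the baseline survey". The abstract repeats "nine months after the intervention (follow-up". Statistical methods {20a} names the purpose of the three-time-point model as "to assess the persistence of treatment effects nine months post-intervention closure". Trial design {8} and Participant timeline {13} place follow-up eight months after endline, and Trial design {8} gives mentoring a length of seven months.

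Table 6 in Participant timeline {13} gives calendar months by cohort:

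| | Baseline | Mentoring | Endline | Follow-up |
|---|---|---|---|---|
| Cohort 1 | Dec 2023 | Jan–Aug 2024 | Oct–Nov 2024 | Jul 2025 |
| Cohort 2 | Feb–Mar 2025 | Apr–Nov 2025 | Dec 2025 | Aug 2026 |
| Cohort 3 | Feb 2026 | Mar–Oct 2026 | Nov/Dec 2026 | June 2027 |

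The October–November 2024 row carries the label "C1 endline assessment (1 mo. after intervention ends", although mentoring in that cohort ends in August. In Table 4 the first primary outcome is "physical, sexual, and/or emotional IPV in the past three months".

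**The concern.** Lag since mentoring is part of what the endline and persistence effects mean. If the calendar gives different lags by cohort, the pooled follow-up effect is not a nine-month effect, and the pooled endline effect is not a one-month effect.

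The lag matters most for intimate partner violence because its recall window is three months. A survey soon after mentoring asks largely about violence while the mentor was still visiting. A survey two to three months later asks largely about violence after the visits stopped. The model in Statistical methods {20a} codes time only as baseline or endline and, as written, has no term for cohort or lag, so the pooled interaction coefficient averages over these different periods. The interim analyses at the Cohort 1 and Cohort 2 endlines and follow-ups would also report results under the same label at different lags.

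**Working it through.** **1. The stated timings agree with each other.** From the text: one month before mentoring + 7 months of mentoring + 1 month after = 9 months from baseline to endline; 9 + 8 = 17 months from baseline to follow-up; 1 + 8 = 9 months from end of mentoring to follow-up. Outcomes {12} is reproduced.

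**2. Table 6 by plain subtraction of month labels** (later month minus earlier month):

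| Interval (months) | Stated | Cohort 1 | Cohort 2 | Cohort 3 |
|---|---|---|---|---|
| Mentoring end to endline | 1 | 2–3 | 1 | 1–2 |
| Mentoring end to follow-up | 9 | 11 | 9 | 8 |
| Baseline to endline | 9 | 10–11 | 9–10 | 9–10 |
| Baseline to follow-up | 17 | 19 | 17–18 | 16 |
| Endline to follow-up | 8 | 8–9 | 8 | 6–7 |

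For example, Cohort 1 runs from Aug 2024 to Jul 2025 = 11 months, and Cohort 3 from Oct 2026 to June 2027 = 8 months.

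**3. Sensitivity to the unknown day.** Table 6 gives no day on which mentoring ends, and each mentoring slot spans eight calendar months for seven months of mentoring. Letting mentoring end anywhere from the first to the last day of its listed month, and follow-up run over its whole listed month, mentoring end to follow-up is 10–12 months in Cohort 1, 8–10 in Cohort 2 and 7–9 in Cohort 3. Cohort 1 misses nine months under every reading.

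**4. The three-month violence window at endline.** For an interview *d* months after mentoring ends, the share of the window inside mentoring is max(0, 1 − *d*/3). On the stated schedule *d* = 1, so the share is 1 − 1/3 = 67%. Averaging day by day over each endline slot in Table 6, with a 91-day window:

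| Assumed end of mentoring | Cohort 1 | Cohort 2 | Cohort 3 |
|---|---|---|---|
| First day of listed month | 9% | 52% | 34% |
| 15th | 19% | 67% | 49% |
| Last day | 34% | 84% | 67% |

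On average Cohort 1 is below half under all three readings and Cohort 2 above half, although only just under the earliest one. Cohort 3 falls on either side. The averages hide some spread: on the last-day reading, Cohort 1 interviews in the first half of October 2024 still cover mostly mentoring time.

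**The case against.** The strongest reply is that this is a reconciliation of a table with its text and little more. Much of that reply stands.

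- Both arms of a cohort are surveyed in the same calendar slot. A reader might infer that the uneven lags bias the treatment comparison; within a cohort they do not.
- A reader might infer that follow-up never falls at nine months. Cohort 2 meets it. With equal cohort weights (an assumption) the mean lag is (11 + 9 + 8)/3 = 9.3 months, so the pooled description is roughly right on average. The average does not describe Cohort 1 or the spread.
- A reader might infer that endline violence is mostly on-mentoring in two cohorts and post-mentoring in the third. This is firm only for Cohort 2 against Cohort 1. Moreover, an on-schedule endline is itself about two-thirds mentoring time, so the clear departure is Cohort 1. Only this primary outcome uses a three-month window; violent discipline uses the past month.
- A reader might infer that cohort differences will be read as effects of programme modifications. The section on modifying allocated interventions {11b} says that cohort effects will be accounted for in the analysis. That is adjustment, and no planned contrast between cohorts is stated.
- A reader might see a flat contradiction between nine months from baseline in Outcomes {12} and "endline data collection occurring roughly 8 months later" in Participant timeline {13}. Counted from the start of the cohort, 7 + 1 = 8 is correct, and the parenthesis after those words supports that reading. The wording is ambiguous and not plainly wrong.

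The text does hedge some intervals with words such as roughly, and the schedule depends on community buy-in. That hedging does not cover a one-month label on a survey two to three months after mentoring, or an 11-month lag described as nine.

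**Conclusion.** The point holds in limited form. By the month labels alone, Table 6 contradicts the timings that define the endline and persistence effects. The Cohort 1 endline is 2–3 months after mentoring despite its one-month label, and its follow-up is at 11 months. Cohort 3 follow-up is at 8 months, and 6–7 months after its endline where eight is stated. Cohort 2 conforms.

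The consequence is for meaning and pooling. The pooled follow-up effect covers about 8–11 months by label (7–12 over all possible days). The pooled endline effect on partner violence combines windows that are mostly post-mentoring in Cohort 1 and, on average, mostly mentoring in Cohort 2. The label results need no assumption. The window shares rest on interviews spread evenly over each listed slot and on an assumed end day, which is why Cohort 3 is left open.

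**What to change.** - Reconcile Table 6 with Outcomes {12}, the abstract and Statistical methods {20a}, and correct the Cohort 1 endline label to the actual lag.
- Describe the persistence analysis as covering about 8–11 months after mentoring, or give the lag by cohort.
- Report actual months since mentoring at each survey, from interview dates and the end of mentoring in the monitoring data. Give control couples the mentoring end date of the paired intervention sub-county in their district. Show endline partner violence by cohort or adjusted for lag.
- State whether "endline data collection occurring roughly 8 months later" counts from the start of the cohort or from baseline, here and in the same wording in Trial design {8}. Leave the separate eight months from endline to follow-up unchanged; it agrees with 17 − 9 = 8.
- For Cohort 3, still ahead at version 1.2, choose one of two courses for the row "C3 follow-up assessment": schedule it to meet the stated nine months (by label July instead of June 2027), or keep June and state the shorter lag.

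The wording and reporting changes cost almost nothing. They assume that interview dates are held in the electronic records, which the article does not say outright. Moving the Cohort 3 wave has a real cost, because controls receive the programme only after follow-up. June 2027 plus seven months of mentoring already reaches about January 2028, past the 2023–2027 project period, and a later survey adds to that delay. The move is therefore optional; stating the true lag is not.
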